#### Active control group: home-exercise

The control group will receive a simplified, guideline-based home-exercise (HE) programme (see online supplemental file 4: home-exercise brochure). The HE programme is prescribed taking into account the key FITT parameters (Frequency, Intensity, Time and Type) consistent with the core exercise-related recommendations of EULAR, ACSM and the German interdisciplinary guideline for FMS.^26 34 36^ Once the intervention period begins, participants will perform the HE programme at home twice per week for 8 weeks (16 sessions in total), with each session lasting approximately 60 min. Each session will comprise three phases. First, there will be 30 min of walking at a pace that is moderately fast and tolerable to the individual. Walking intensity will be prescribed using the Talk Test, in line with guidance for monitoring aerobic exercise intensity.^45^ Second, there will be 15 min of strength exercises (2–3 sets of 8–12 repetitions with body weight and/or tolerable external load) targeting the back extensor muscles, core stabilisation muscles, shoulder-girdle muscles of the upper extremity and hip and knee muscles of the lower extremity; no structured progression will be implemented. Thirdly, there will be 15 min of stretching exercises for the neck muscles, pectoralis major/minor, erector spinae, hamstrings and quadriceps femoris (one to two repetitions of 30 s each).

In order to enhance safety and feasibility, participants will be instructed in symptom-contingent pacing and pain flare. If pain markedly increased or a flare occurred, participants will be advised to reduce exercise dose (by decreasing range of motion, sets/repetitions, walking pace/duration or by selecting easier variations). They will also be advised to temporarily pause if necessary and to resume at the previously tolerated level once symptoms have stabilised.

In addition, as an incentive to enhance adherence in the control group, participants will be offered 6 PYM intervention sessions after completion of all trial measurements.

### Adverse events and adherence of interventions

Adverse events will be measured through predefined items in exercise diaries for both groups. Individuals in both intervention and control groups will receive the exercise diary every 2 weeks via an emailed REDCap link (see onlinesupplemental files 5  6: Intervention/Control Group Exercise Diary). They will complete it retrospectively for the preceding four exercise sessions and submit it electronically through REDCap. If no email address is available, the diary will be sent/returned by post and responses will be entered into REDCap by the study team. Subsequently, all intervention-related events will be reviewed by the study team and classified according to predefined criteria including intervention context (supervised PYM vs HE), event type (physical, psychological, other) and seriousness (serious vs non-serious).

The conditions of patients experiencing adverse effects due to the study interventions will be evaluated and referred for additional treatment if necessary.

Adherence to the PYM intervention will be assessed by recording the number of supervised PYM sessions attended and by using participant exercise diaries for HE, in which twice a week, duration and components of the prescribed exercises are recorded.

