#### Intervention group: supervised PYM sessions+home exercise

Intervention group participants will receive both the supervised PYM intervention and an unsupervised home-exercise programme (see detailed description: Active Control Group). Participants in the intervention group will be divided into two subgroups of up to 10 participants. Each subgroup will attend 16 supervised PYM sessions over 8 weeks (two times per week, 75 min per session) and complete 16 HE sessions in the same period (two times per week, 60 min per session). This subgroup division is intended to facilitate appropriate modification of the practice to participants’ individual limitations and to allow closer observation during the PYM sessions. In addition, the intervention will be delivered in successive cohorts, with short gaps between cohorts to accommodate assessment scheduling. The sessions will follow the structure outlined in table 1, and verbal and tactile adjustments will be made if necessary.

**Table 1 T1:** PhYoMind intervention structural framework

PhYoMind intervention			
At the beginning of each session, setting an intention and inviting practice accordingly			
1.	Body tapping, full body shaking, dynamic warm-up sequences or easy sun salutations		10 min
2.	Standing poses	Physiotherapy techniques will be used in yoga poses: *Self-proprioceptive neuromuscular facilitation techniques*****, self-nerve gliding techniques**†**, self-mobility exercises**‡*	40 min
3.	Back bend-focused poses		
4.	Forward bend-focused poses		
5.	Three block poses (hip openers/strengtheners, core strengtheners, spinal rotation or balance-oriented poses)		
6.	Inversion pose (legs up the wall pose)		2 min
7.	Breathing practices (alternate/left nostril breathing and humming bee breathing)		8 min
8.	Mindfulness meditation		5 min
9.	Shavasana pose with post isometric relaxation§		10 min

* Contract-relax technique, contract-relax antagonist contract technique.

† Median nerve, ulnar nerve, radian nerve, sciatic nerve, femoral nerve gliding.

‡ Shoulder, spine and hip mobility exercises.

§ Sequential submaximal isometric contractions of major muscle groups from feet to head, followed by one whole body squeeze-release, then resting in Shavasana.

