### Statistical analysis

The data obtained during the study will be analysed using the statistical software R, V.R-4.3.3 for Windows. Descriptive statistics including mean, SD, median, etc, will be calculated for demographic and clinical characteristics in both groups. Repeated Measures ANOVA (rmANOVA) will be used to analyse the effect of time, intervention group and their interaction on primary and secondary outcomes. Time will be considered as the within-subject factor and group will be considered as the between-subject factor. Effect sizes and group differences will be reported subsequently. The significance level will be p<0.05.

To ensure the robustness and validity of the statistical analysis, missing data will be addressed using multiple imputation. All randomised participants will be included in the main analyses according to the intention-to-treat principle and will be analysed in the groups to which they were originally allocated. Serious and non-serious adverse events and drop-outs during the intervention period will be summarised and compared between groups using absolute and relative frequencies. Given the relatively limited sample size, no formal mediation analysis is planned as part of the confirmatory or secondary statistical analyses. Associations between fibromyalgia severity, perceived stress and clinical outcomes may be explored descriptively or in exploratory regression models, but these analyses will be considered hypothesis-generating and interpreted with caution. No formal interim analyses are planned, and no predefined stopping rules for efficacy or futility have been established.

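### One adverse-event diary window of four sessions is set for both arms: it fits the control arm's fortnight but not the intervention arm's eight sessions, and it conflicts with the Table 2 footnote

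*Protocol article*

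**What the plan says.** The section on adverse events and adherence makes the diary the measuring instrument for harms: "Adverse events will be measured through predefined items in exercise diaries for both groups". On timing, "Individuals in both intervention and control groups will receive the exercise diary every 2 weeks via an emailed REDCap link". On the recall window, "They will complete it retrospectively for the preceding four exercise sessions and submit it electronically through REDCap". The same section refers to a separate diary form for each arm; both are supplements and are not shown.

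The intervention section prescribes "16 supervised PYM sessions over 8 weeks (two times per week, 75 min per session) and complete 16 HE sessions in the same period". The active-control section prescribes the HE programme alone, twice a week for 8 weeks, 16 sessions in total.

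The Table 2 footnote on adverse events and adherence describes the window differently. Monitoring is continuous, and the diary reviews at weeks 2, 4, 6 and 8 each look back over the interval just ended.

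On handling, the adverse-event section says that "all intervention-related events will be reviewed by the study team and classified according to predefined criteria". The criteria are context (PYM or HE), event type and seriousness. The Statistical analysis section then says: "Serious and non-serious adverse events and drop-outs during the intervention period will be summarised and compared between groups". That sentence has no restriction by relatedness.

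**The concern.** A recall window expressed as a number of sessions gives equal coverage only if both arms do the same number of sessions between diaries. Here they do not. The four-session window spans a control participant's whole fortnight, but only half of the sessions prescribed to an intervention participant. The diary is the named source of adverse-event data, so a window that captures a different share of exposure in each arm can distort the comparison of harms. Assessing the safety of both interventions is a stated aim in the Introduction.

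The second issue is a mismatch between data handling and analysis. If review and classification, including for seriousness, apply to events considered intervention-related, the protocol gives no route by which other events acquire the serious or non-serious label that the planned comparison needs. The Ethics approval section likewise undertakes to report serious or unknown events to the committee without a relatedness condition. Any attribution judgement is also made in a trial where participants and the physician delivering PYM cannot be blinded.

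The article says that recruitment has begun, so an event missed by a diary completed with too narrow a window may not be recoverable later.

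**Working it through.** **Inputs.** Diary window: 4 sessions. Diary interval: 2 weeks. Both come from the adverse-event section. Intervention arm: 2 PYM and 2 HE sessions a week for 8 weeks (intervention section). Control arm: 2 HE sessions a week for 8 weeks (active-control section). Planned size: 20 per arm (Sample size estimation).

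**Step 1: reproduce the stated four.** Sessions per diary = sessions per week × 2 weeks.
- Control: 2 × 2 = 4. This matches the stated window.
- Intervention: (2 + 2) × 2 = 8. This does not.

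**Step 2: coverage over the trial.** Number of diaries = 8 / 2 = 4. Sessions inside the windows = 4 × 4 = 16. Prescribed sessions: control 2 × 8 = 16, intervention 4 × 8 = 32.

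**Step 3: coverage under each reading of the text.**

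| Reading | Control | Intervention |
|---|---|---|
| Last four sessions of any kind | 16/16 (100%) | 16/32 (50%) |
| Last four HE sessions | 16/16 HE | 16/16 HE, 0/16 PYM |
| Whole preceding interval (Table 2 footnote) | 16/16 | 32/32 |

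Only the third reading covers all sessions in both arms, and it is not what the adverse-event section says. The second reading leaves every PYM session outside the stated window, although that section plans to classify events as arising from PYM or from HE.

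**Step 4: what the first reading could do to the counts.** This is an illustration only. The per-session event risk p is not in the documents and is varied from 0.01 to 0.10. It is taken as equal in every session and independent between sessions. Events are assumed to be tied to single sessions, and participants are assumed to leave out anything beyond the last four. Expected events per arm = 20 × sessions × p. Share of participants with at least one event = 1 − (1 − p)^sessions.

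| p | Control events | Intervention events, all | Intervention events, in window | Control, ≥1 event | Intervention, ≥1 event, all |
|---|---|---|---|---|---|
| 0.01 | 3.2 | 6.4 | 3.2 | 14.9% | 27.5% |
| 0.02 | 6.4 | 12.8 | 6.4 | 27.6% | 47.6% |
| 0.05 | 16 | 32 | 16 | 56.0% | 80.6% |
| 0.10 | 32 | 64 | 32 | 81.5% | 96.6% |

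For example, at p = 0.02: 20 × 16 × 0.02 = 6.4 and 20 × 32 × 0.02 = 12.8. Under these assumptions a 2:1 ratio of events would be recorded as 1:1, and the in-window share of intervention participants with an event would equal the control share. Under the whole-interval reading nothing is lost.

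**Step 5: the relatedness wording.** Set side by side, the adverse-event section describes review and classification for intervention-related events, while the Statistical analysis section compares serious and non-serious events with no such condition. The second cannot be carried out for all reported events unless all of them are classified.

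**The case against.** The best defence is that the adverse-event sentence is loosely worded and the practice is sound. The Table 2 footnote covers the whole interval, and the timeline section has both groups monitored from week 0. Four is also the fortnight's HE count in both arms. The adverse-event section takes HE adherence from the diary and PYM adherence from attendance records, so the four sessions may mean HE sessions only. PYM is named as a context for classification, so its events are clearly meant to be captured, and the intervention arm has its own form, which may already ask about PYM. All of this stands as evidence of intent. It does not make the stated window correct: it shows that the article describes the window in ways that cannot all hold.

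A reader might infer more than the text supports, in three ways.

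- *That about half of the intervention arm's events will be lost.* This needs the assumptions of Step 4, none of which the documents confirm, and the intervention-arm diary is not shown.
- *That the plan makes PYM look safer than it is.* The direction is open. Intervention participants are seen twice a week by a physician, in subgroups formed partly for closer observation, while control exercise is unsupervised. That could raise detection under PYM. The relatedness wording is the same for both arms.
- *That the PYM instructor decides which events count and that unrelated events are discarded.* The article assigns review to the study team. It does not say who judges relatedness, whether the instructor takes part, or that other events are dropped.

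It is also fair to say that the layout of safety tables and rates per session can be left to the statistical analysis plan. The recall window and the set of events to be classified are different, because they determine what is collected.

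**Conclusion.** The point holds as an inconsistency in how adverse events are ascertained and classified. The session counts are certain from the protocol: 4 against 8 per fortnight, and 16/16 against 16/32 covered over 8 weeks if the four-session rule is followed literally. That rule conflicts with the Table 2 footnote and can cause differential ascertainment. Whether it does depends on the unseen arm-specific diaries and on how participants complete them, so neither a size nor a direction of bias can be given. The gap between classifying intervention-related events and comparing serious and non-serious events without that limit is a further, smaller inconsistency in the text. Because safety is a stated aim and correction is cheap, the passages should be reconciled.

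**What to change.** Reconcile the intervention section, the adverse-event section, the Table 2 footnote and the Statistical analysis section so that they state the same rule:

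1. In both arms, the adverse-event items of each diary cover the whole preceding 2 weeks. In the intervention arm this includes all PYM and all HE sessions, eight per fortnight as prescribed. Check the intervention-arm diary against this and amend it if it is narrower.
2. Every reported event is classified for type and seriousness, whatever its judged relation to the intervention.
3. All reported events enter the between-group comparison, with relatedness shown separately.

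The cost is a short edit to the text, possibly one form, a slightly longer diary for intervention participants and a little more classification work. Sample size, visits and the efficacy analysis are unaffected. If diaries have already been completed under a narrower window, the date of the change should be recorded so that the safety data before and after it can be told apart.

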### Outcomes

As a primary outcome, the Fibromyalgia Impact Questionnaire (FIQ) will be used to assess participants’ functional disability before and after the intervention.^46^ The FIQ is a valid and reliable questionnaire with a total score ranging between 0–100 and measuring overall impact, including symptom severity, functionality, work difficulties, morning fatigue, depression, anxiety and general well-being rated by individuals with fibromyalgia. Higher scores indicate a greater impact of symptoms.^47^

Secondary outcomes will be measured using the following tools, with the following parameters being collected: Central Sensitisation Inventory (CSI),^48^ 20-item Multidimensional Fatigue Index (MFI-20),^49 50^ Pittsburgh Sleep Quality Index (PSQI),^51^ Perceived Stress Scale (PSS)^52^ and Visual Analogue Scale (VAS) for current, average and worst pain intensity of the participants over the last week.^53^

As a secondary outcome, changes in the autonomic nervous system will also be objectively recorded by measuring HRV. It will be measured and recorded with a Polar H10 (Polar Electro UK, Warwick, UK) chest strap using the validated Elite HRV mobile application, which has ease of use, reliability, data recording, storage, analysis and export features.^54^,^56^ The Polar H10 chest strap is CE certified and meets the EU requirements for non-invasive physiological data measurements. Participants will be requested to sit in silence for a period of 5 min, after which a 5-minute recording will be made for the purpose of analysis. During the HRV recording, participants will remain seated and quiet, with no physical activity. Breathing rate and depth will not be controlled. With the Polar H10 chest strap device, minimum-maximum-average Heart Rate (HR), HRV parameters: RMSSD (Square Root of the Mean of the Sum of the Squares of the Differences between RR Intervals), SDNN (Mean and SD of RR Intervals), total power, mean R-R interval, HF (High Frequency), LF (Low Frequency), LF/HF, (with their log-transformed indices lnRMSSD, lnHF, lnLF) will be collected and recorded in the Elite HRV application and manually entered into REDCap system.

Further assessments, as part of the initial measurement and questionnaire administration, demographic data of the participants will be collected. These data include age, sex, marital status, educational status, working status, duration of fibromyalgia and any relevant health conditions (other than exclusion criteria).

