**Methods and analysis:**

This monocentric study uses a parallel-group (1:1) randomised controlled design, in which the outcome assessor and statistician are blinded to group allocation. Individuals with a clinical diagnosis of FMS (n=40) will be included in the study (Cohen’s f=0.675; α=0.05; power=0.80). Participants will be randomised to receive either PYM intervention in addition to Home Exercise (HE) programme or HE programme alone. The intervention period for both groups will last 8 weeks; PYM sessions will be held twice a week for 75 min each. The primary outcome is the broad disease impact and functional impairments measured by the total score of the Fibromyalgia Impact Questionnaire. Secondary outcomes include central sensitivity, as assessed by the Central Sensitisation Index; autonomic nervous system function, as measured objectively by heart rate variability; pain perception (current, average, worst), as assessed by the Visual Analogue Scale; fatigue, as assessed by the Multidimensional Fatigue Inventory; stress, as assessed by the Perceived Stress Scale; and sleep quality as assessed by the Pittsburgh Sleep Quality Index. Adherence and adverse events will be assessed for both interventions. Repeated measures ANOVA will be used to analyse the effect of time, intervention group and their interaction on primary and secondary outcomes under an intention-to-treat principle.

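### Only the PYM arm practises breathing techniques, so a T2 group difference in RMSSD, HF, LF or LF/HF under free breathing cannot be separated from altered breathing unless the breathing rate is reported

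*Protocol article*

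**What the plan says.** The Abstract lists as a secondary outcome "autonomic nervous system function, as measured objectively by heart rate variability". The Outcomes section repeats the claim: "changes in the autonomic nervous system will also be objectively recorded by measuring HRV".

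The recording conditions are in the same section: "Participants will be requested to sit in silence for a period of 5 min, after which a 5-minute recording will be made". Participants stay seated and quiet, and "Breathing rate and depth will not be controlled". The parameters are minimum, maximum and average heart rate, RMSSD, SDNN, and "total power, mean R-R interval, HF (High Frequency), LF (Low Frequency), LF/HF, (with their log-transformed indices lnRMSSD, lnHF, lnLF) will be collected". Neither this list nor the standardised conditions under Data collection and management (quiet room, seated, brief rest, artefact limit) mention a respiratory measure.

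Table 1 gives every PYM session an 8-minute block: "Breathing practices (alternate/left nostril breathing and humming bee breathing"). On dose, the protocol says: "Each subgroup will attend 16 supervised PYM sessions over 8 weeks (two times per week, 75 min per session"). The home-exercise programme, which both arms receive, consists of walking, strength and stretching (Active control group section).

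The Statistical analysis section applies repeated measures ANOVA to all primary and secondary outcomes. The limitations in the Discussion do not mention breathing.

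**The concern.** RMSSD and the spectral indices depend on how a person breathes during the recording. One arm trains breathing and the other does not. If PYM participants sit and breathe differently at T2, these indices can move without any change in the autonomic modulation that the protocol means to measure. Randomisation does not remove this, because the difference arises after allocation.

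What is at stake is the meaning of a secondary result. The FIQ, CSI, MFI-20, PSQI, PSS and VAS are all self-reported by participants who know their allocation. HRV is the one efficacy outcome that is not, so a group difference in it is likely to be cited as objective support. The wording that HRV objectively records autonomic change is stronger than the planned measurement can carry for the breathing-sensitive indices.

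**Working it through.** **1. Exposure to breathing practice, from the protocol.**
- The Table 1 blocks add up to the stated session length: 10 + 40 + 2 + 8 + 5 + 10 = 75 min.
- PYM arm: 8 min × 16 sessions = 128 min of breathing practice.
- Control arm: 0 min listed.

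**2. Sensitivity of the indices.** The protocol gives no figure for this, so what follows is an illustration. All its inputs are assumptions:
- mean RR Δ = 0.85 s;
- a respiratory oscillation of amplitude A = 30 ms at breathing frequency f;
- a second oscillation of 15 ms at 0.1 Hz;
- bands LF 0.04–0.15 Hz and HF 0.15–0.40 Hz, so breathing below 0.15 × 60 = 9 breaths/min leaves the HF band.

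Only f is changed.

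Power of a sine is A²/2: respiratory 30²/2 = 450 ms², slow oscillation 15²/2 = 112.5 ms². The respiratory power falls in HF at 9 breaths/min or more and in LF below that.

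For a sine sampled every Δ seconds, its RMSSD component is √2 · A · sin(π f Δ), and the two components add as squares.
- Slow oscillation: √2 × 15 × sin(π × 0.1 × 0.85) = 5.60 ms.
- 15/min (f = 0.25): √2 × 30 × 0.6191 = 26.27; √(26.27² + 5.60²) = 26.9 ms.
- 8/min (f = 0.1333): √2 × 30 × 0.3486 = 14.79; √(14.79² + 5.60²) = 15.8 ms.

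A finite 300-second series gives practically the same values:

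| Breaths/min | RMSSD (ms) | HF (ms²) | LF (ms²) | SDNN (ms) | Mean RR (ms) |
|---|---|---|---|---|---|
| 15 | 26.8 | 450 | 112 | 23.7 | 850 |
| 12 | 22.3 | 450 | 112 | 23.7 | 850 |
| 10 | 19.1 | 450 | 112 | 23.7 | 850 |
| 8 | 15.8 | about 0 | 562 | 23.7 | 850 |

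From 15 to 8 breaths/min RMSSD falls by 1 − 15.8/26.8 = 41%. LF/HF is 112/450 = 0.25 at 15/min and becomes very large at 8/min. HF and LF change only when the rate crosses 9/min, whereas RMSSD already falls between 15 and 10. SDNN = √(450 + 112.5) = 23.7 ms throughout.

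**3. Second set of assumptions.** With a 40 ms respiratory amplitude, a 20 ms slow oscillation at 0.09 Hz and added noise, going from 15 to 8 breaths/min gives RMSSD 37 to 24 ms, HF 609 to 19 ms² and LF/HF 0.33 to 51. Mean RR (849 ms) and SDNN (33 ms) do not change.

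**4. Depth.** Under the first set at 15/min, if deeper breathing raised the amplitude from 30 to 40 ms, HF would become 40²/2 = 800 ms² and RMSSD √((√2 × 40 × 0.6191)² + 5.60²) = 35.5 ms. SDNN would rise as well, to √(800 + 112.5) = 30.2 ms. A change in rate alone lowers RMSSD; a change in depth can raise it. The direction of any shift is therefore not predictable from the protocol.

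**The case against.** The strongest reply is that altered breathing is part of what PYM does. The secondary objective is to compare the effects of PYM plus home exercise with home exercise alone, not effects net of breathing. The Introduction presents PYM as one integrated package that targets autonomic regulation. The Statistical analysis section rules out formal mediation analysis, and the Discussion leaves single components to later trials. This stands: a reader might infer that the HRV comparison is confounded or invalid, and it is not. It estimates the effect of PYM on resting HRV under free breathing. What the documents do not support is going from there to a change in autonomic function without knowing whether breathing changed too.

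Second, nothing says that participants learn slow breathing for use at rest. Breathing takes 8 of 75 minutes, T2 falls in the week after the programme, assessments are held apart from sessions, and 5 minutes of silence precede the recording. This stands as to likelihood: the number who would breathe differently is unknown. It is also the reason to look.

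Third, with fixed depth slower breathing can only lower RMSSD, so it could not produce a false rise. That is correct for rate alone; a rise needs greater depth, and the protocol leaves depth uncontrolled as well.

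Fourth, a reader might infer that breathing is definitely not recorded, or that every HRV index is compromised. The first is only inferred from a detailed parameter list in a condensed article, and the written instructions and assessor checklist are not shown. The second is wrong: mean RR and heart rate did not move with breathing rate, nor did SDNN at 8–15 breaths/min with depth unchanged.

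**Conclusion.** The point holds as a cheap improvement to a secondary outcome. It is not an error that invalidates an analysis. The documents show breathing practice in one arm only, breathing expressly uncontrolled during HRV, no respiratory rate among the listed parameters, and an autonomic reading of the result. As described, a T2 difference in RMSSD, HF, LF or LF/HF could not be separated from altered breathing.

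The size is illustrative only. A drop of about 40% in RMSSD and the loss of HF power between 15 and 8 breaths/min rest on assumed amplitude, mean RR and frequency bands, and apply to a participant who slows that far. The average effect in the arm depends on how many do so, which the documents do not say. It would be too strong to conclude that the autonomic objective goes unanswered, since the randomised contrast is valid and some listed indices are robust to breathing rate. The FIQ conclusion is unaffected.

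**What to change.** Keep free breathing and keep the main analysis. In addition:

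1. Retain the exported RR series of each existing 5-minute recording. The protocol credits the application with export features, but says that indices are entered into REDCap by hand. Recruitment has begun, so it should be confirmed now that the series are kept; otherwise the rate may not be recoverable later.
2. Derive the breathing rate at T0 and T2 and report it by arm beside the HRV results. If it is already captured, it is enough to say so.
3. State in advance that, if breathing rate differs between arms, differences in RMSSD, HF, LF and LF/HF will be described as effects on resting HRV that may run through breathing, not by themselves as a change in autonomic function.
4. Label any analysis that adjusts for breathing rate or excludes recordings by it as exploratory. It conditions on a post-randomisation variable and, with 20 per arm, could unbalance the groups. Excluding only recordings below 9 breaths/min would also miss the RMSSD shift above that rate. Such an analysis should not decide the claim.

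The cost is one extra field per recording and a more cautious interpretation. A rate taken from the RR series is an estimate and says little about depth, so some ambiguity remains even when the rates agree.
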